#### Fatigability during the cognitive task

3.4.5

Fatigability during the cognitive task (Research Question 2) will be quantified as reported by Hassan et al. (2024) using the balanced integration score (BIS) (Liesefeld & Janczyk, 2019). The AX‐CPT was chosen as the task in which to measure task performance, and therefore it will be presented first and last, following the protocol of Hassan et al. (2024). The BIS will be calculated using the reaction time and response data during the first and last repeat of the AX‐CPT task. The BIS combines reaction time and accuracy into a single metric which is standardized across all time points and participants. A BIS score of zero represents an average level of performance across all participants and conditions, with above average and below average performance indicated by positive and negative numbers, respectively. The code used to calculate the outcome measure is available at https://github.com/Liesefeld/BIS.

#### Fatigability during the physical task

3.4.6

Fatigability during the 6MWT (Research Question 2) will be quantified as the change in average walking speed (m/s) from the beginning (30−60 s) to the end (330−360 s) of the test (Andersen et al., 2016; Witherspoon et al., 2018). The first time point will be taken after the initial 30 s to avoid confounding from acceleration. Example data and the code used to calculate fatigability in during the 6MWT are provided as Supporting information.

#### Somatosensory processing

3.4.7

Two measures of somatosensory processing will be evaluated at each of the pre‐ and post‐task time points: a measure of somatosensory attenuation and a measure of somatosensory gating.

##### Somatosensory attenuation

The somatosensory attenuation assessment is expected to take 10 min. Participants will be seated comfortably and positioned with their dominant hand placed on a table with their palm facing upwards. Participants will be given a practice trial to make sure they understand the task.

An audible beep will mark the start of the trial. The researcher ([name]) will press on the abductor pollicis brevis muscle of the dominant hand with a Digital Handheld Dynamometer (microFET2; Hoggan Scientific, Salt Lake City, UT, USA). The force will be applied through a digit transducer pad of 1 cm diameter to a magnitude of 4, 5, 6 or 7 N, and will be maintained for 3 s until a second beep marks the end of the 3 s. This constitutes an exafferent force. The magnitude of force applied is displayed in real time on the device and will be visible to the researcher, but not to the participant. After 2 s rest, a third beep will sound, and the participant will be asked to press the same probe onto the same section of skin with the same force that was exerted by the researcher with a second Digital Handheld Dynamometer (microFET2, Hoggan Scientific). This constitutes a reafferent force (Kilteni & Ehrsson, 2022).

Following a practice trial, each force level (4, 5, 6 or 7 N) will be performed eight times, for a total of 32 trials. These trials will be organized in two blocks of 16 trails. The force level will be randomized within MATLAB software. There will be an interval of 60 s between the two blocks. The average force across the 3 s is stored in the dynamometer for each trial and will be retrieved after the end of the session.

Somatosensory attenuation will be quantified as the mean force overcompensation between the exafferent force (generated by the researcher) and the reafferent force (generated by the participant). Mean force overcompensation will be calculated as the average difference between the exafferent and reafferent force (Wolpe et al., 2018), on each trial (*n* = 8) across each force level (*n* = 4). To examine force matching as a function of force level, the intercept and slope from the linear regression between exafferent and reafferent force will be calculated for each participant and condition. Example data are shown in Supporting information Figure S3, and the code used to calculate the outcome measure is provided as Supporting information.

##### Somatosensory gating

The protocol to evaluate somatosensory gating replicates that of Baker et al. (2023) to allow direct comparison of results and is expected to take 20 min. The participant will be seated comfortably and positioned with their dominant hand placed on a table.

The index finger of the dominant hand will be stimulated with single, constant current, square wave pulses of 2 ms duration by a constant current stimulator (model DS7A; Digitimer; Welwyn Garden City, UK) connected to adhesive surface electrodes (71505‐K/C/12; Ambu Ltd, Alconbury Weald, UK) placed on the proximal and middle phalanges.

Stimulation will be mild, starting below perceptual threshold and rising to the threshold at which it can just be perceived, but never above this. At this threshold, the stimulation feels like a mild transient ‘tingle’. Perceptual threshold will be determined prior to the task by asking participants to report verbally when they feel a stimulation on their index finger. The initial stimulus intensity will be 0.10 mA. Based on previous work (Chapman et al., 1987), we expect this to be imperceptible to all participants. The intensity will be adjusted using an ascending–descending–ascending staircase method as follows:
A set of up to six stimuli will be delivered at the initial intensity. If the participant does not report perceiving a stimulus on at least three out of six trials, stimulation intensity will be increased by 0.10 mA for the next set. This continues until the participant reports that they perceive a stimulus on at least three out of six trials.At this point, the stimulus intensity is then decreased by 0.05 mA per set until the participant does not report perceiving a stimulus on three out of six trials.The stimulation intensity is then increased by 0.01 mA per set until the participant again reports that they perceive a stimulus on three out of six trials. This value is recorded as the perceptual threshold.

Based on previous work (Baker et al., 2023; Chapman et al., 1987) it is anticipated that perceptual threshold will range from 0.23 to 1.11 mA across participants.

One hundred trials will then be performed, during which participants will be given a stimulus (*P* = 0.8) or not (*P* = 0.2). Fifty of these will be ‘resting’ trials, and 50 will be movement trials. In a resting trial, participants will be asked if they are ready, and asked to report if they felt a stimulation or not. In a movement trial, participants will be asked if they are ready, and then instructed to make a rapid index finger abduction movement and report if they felt a stimulation or not. Stimulation will have been delivered in 80% of the trials. Activity of the first dorsal interosseus muscle will be monitored using surface electromyography (Delsys Trigno Quattro Sensor) and monitored in real time in D‐flow software (Motek Medical). The software will be programmed to detect when the muscle activity starts to increase above baseline and will deliver a stimulus (*P* = 0.8) or not (*P* = 0.2) 50 ms after this onset of muscle activity. In this way, the timing of the stimulus in the movement trials is directly linked to movement onset. In all trials, participants will be given up to 5 s to respond if they felt stimulus or not. If they are unable to respond, this will be reported as stimulus not perceived.

Rest and movement trails (*n* = 50 of each) will be randomized. Stimulus intensity will start at the pre‐determined perceptual threshold and will subsequently be controlled in equal steps separately for rest and movement trials (Baker et al., 2023). If the participant perceives the stimulus, it will be decreased by 0.02 mA for the next trial in that condition. If the participant does not perceive the stimulus, it will be increased by 0.02 mA for the next trial in that condition. There will be an inter‐stimulus interval of at least 3 s between consecutive trials.

Somatosensory gating will be quantified in the same way as reported by Baker et al. (2023), using code provided by these authors. The probability of detection at intensity *I* will be fitted to a sigmoid curve:

$$P\left(\mathrm{Detection}\;\mathrm{at}\;\mathrm{intensity}\;I|I_{50},k\right)=\frac{1}{1+exp[\left(I_{50}-I\right)/k)]}$$
where *I*
_50_ is the intensity with 50% detection, and *k* determines the slope of the curve. This will be quantified in rest and movement trials, and somatosensory gating is *I*
_50_movement_ − *I*
_50_rest_. Example sigmoid curves calculated at rest and during movement are shown in Supporting information, Figure S4.

### Data inclusion and exclusion

3.5

Participants failing to complete the cognitive task will be excluded from the analysis for Research Question 2, 3 and 4 as we will not be able to compare the impact of task. However, their data will be included in other exploratory analysis where the cognitive task is not included as a predictor. Participants who do not complete the post‐task measures in either session, due to withdrawing from the study, will be excluded from the analysis for Research Question 3.

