**FIGURE 2 eph13615-fig-0002:**
[figure not shown]
Data collection timeline. HRV, heart rate variability. JISC is a digital platform designed specifically for education and research organizations that can be used for the creation and dissemination of surveys. BL, baseline; PRE‐1, immediately after pre‐task somatosensory gating measure; PRE‐2, immediately after pre‐task somatosensory attenuation measure; POST‐1, immediately after the completion of the task (cognitive or physical); POST‐2, immediately after post‐task somatosensory gating measure; POST‐3, immediately after post‐task somatosensory attenuation measure.

On completion of the participant characteristics and validated measures, participants will be given a unique, randomly generated four‐digit identifier. Consent forms, which will contain the participants personal details, will be saved separately from all other data and only identified with the participants four‐digit identifier.

The protocol is split into two testing sessions. Each session is expected to take up to 90 min. The two sessions are identical, except that in one session participants perform a cognitive task and in the other session they perform a physical task. Participants will be asked to complete both sessions in a crossover design. In each session, somatosensory processing (attenuation and gating) will be measured pre‐ and post‐task (physical or cognitive). The order of the two sessions will be randomized using the command randi([1 2]) in MATLAB software version 23.2 (MathWorks Inc., Natick, MA, USA), which will be run on the morning of the first testing session. A value of ‘1’ indicates that cognitive task will be performed first and ‘2’ indicates that the physical task will be performed first. Participants will be asked to return on a separate day for each session.

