In the original study (Hassan et al., 2024), each cognitive task was performed for 10 min at a time and was repeated three times, resulting in a total duration of 2 h (four tasks × 10 min per task × three repeats = 4 × 10 min × 3 = 120 min). In the present study we will reduce the duration of each task to 2 min, giving a total duration of 24 min (four tasks × 2 min per task × three repeats = 4 × 2 min × 3 = 24 min). This has been done in consultation with our patient and public involvement group to avoid placing excessive burden on a population that reports high fatigue levels. The modified duration is expected to induce fatigue as participants are required to task switch between multiple short‐duration tasks, constituting an additional demand that increases cognitive fatigue (Dang et al., 2013). Testing of this modified task in 15 young healthy individuals indicates a significant increase in fatigue from pre‐ to post‐task. Fatigue measured on a 100 mm visual analogue scale (VAS) increased from a mean (standard error) of 26 (5) mm pre‐task to 59 (5) mm post‐task (Student's paired *t*‐test *t* = −7.251; *P* < 0.001). Fatigue measured using the fatigue subscale of the Brunel Mood Scale increased from a median (interquartile range) of 7.0 (1.5) pre‐task to 9.0 (4.0) post‐task (Wilcoxon signed rank test *Z* = 2.991; *P* = 0.003) ([name] and [name], unpublished data; Figures 3 and 4). Participants will be sent a training version of this protocol prior to attending the lab session, and this will allow them to familiarize themselves with the tasks involved to minimize any learning effect during the testing session. The cognitive task will be completed on a computer that will be placed in front of participants. Full details of the task are in Supporting information, Appendix 2.

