Hypothesis 2: State fatigue following exertion will be predicted by somatosensory attenuation at baseline, somatosensory gating at baseline, the presence of long COVID (long covid/controls), and the type of task (cognitive/physical). Performance fatigability will be considered a moderator variable in these relations. State fatigue prior to exertion will be included as a covariate in this analysis.

This will be tested using a linear mixed model:

$$Y_{ijk}=\mu +a_{i}+b_{j}+c_{k}+d_{ik}+e_{ik}+f_{ik}+g_{ijk}+\left(f_{ik}\times a_{i}\right)+\left(f_{ik}\times b_{j}\right)+\varepsilon_{ijk}$$
where:

*Y_ijk_
*: state fatigue following exertion in the *i*‐th group (long COVID/control) during task *j* (cognitive/physical) for the *k*‐th subject.μ: the overall mean of state fatigue following exertion.
*a_i_
*: the effect of the *i*‐th group (fixed effect: long COVID vs. control).
*b_j_
*: the effect of the *j*‐th task (fixed effect: cognitive vs. physical).
*d_ik_
*: the baseline somatosensory attenuation for the *k*‐th subject in the *i*‐th group.
*e_ik_
*: the baseline somatosensory gating for the *k*‐th subject in the *i‐*th group.
*f_ijk_
*: the performance fatigability for the *k*‐th subject in the *i*‐th group during the *j*‐th task.
*g_ijk_
*: the state fatigue prior to exertion for the *k*‐th subject in the *i*‐th group during the *j*‐th task (covariate).(*f_ik_
*×*a_i_
*): the interaction term between performance fatigability and group.(*f_ik_
*×*b_j_
*): the interaction term between performance fatigability and task.
*ϵ_ijk_
*: the residual error term, assumed to be normally distributed.
Hypothesis 3: The change in somatosensory attenuation (Research Question 3a) and somatosensory gating (Research Question 3b) from pre‐ to post‐task will be predicted by the change in state fatigue from pre to post, fatigability, the presence of long COVID (long COVID/controls), and the type of task (cognitive/physical).

We will use linear mixed models to test these hypotheses, with separate models for somatosensory attenuation and somatosensory gating:

$$Y_{ijk}=a_{i}+b_{j}+c_{ijk}+d_{ijk}+u_{0i}+\varepsilon_{ijk}$$
where:

*Y_ijk_
*: attenuation or gating at baseline in the *i*‐th group (long COVID/control) during task j (cognitive/physical) for the k‐th subject.
*a_i_
*: the fixed effect of the *i*‐th group (long COVID vs. control) on baseline attenuation.
*b_j_
*: the fixed effect of the *j*‐th task (cognitive vs. physical) on baseline attenuation.
*c_ijk_

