### Sample size

3.8

The study is powered to address Research Question 1a. Previous research indicates an effect size of 0.78 for differences in somatosensory attenuation between young and older individuals (Parthasharathy et al., 2022). Powering the current study to detect an effect size of 0.78 between two independent means for Research Question 1a—somatosensory attenuation in individuals with and without long COVID—with an α error probability of 0.05 and a power of 95% and based on a non‐directional two‐tailed hypothesis requires 44 participants per group (G*power 3.1.9.7). Dropout is not expected to impact Research Question 1a or 1b, as it involves initial measurements during the first session. However, there is a potential for dropout to impact the subsequent research questions, which rely on participants returning for a second session.

The sample size gives us power of 90% to detect an effect of 0.70 between two groups at two repeated time points with alpha error probability of 0.05 for Research Questions 2 and 3, or a power of 80% to detect an effect of 0.60. A dropout rate of 10% would mean that our power to detect these effect sizes decreases to 60%. The approach for addressing Research Questions 2 and 3 ensures that the study is adequately powered to detect correlations of 0.50 and 0.40, respectively. The code used to calculate the outcome measure is available at https://github.com/smancuso/R‐ Code/blob/cc90c623c4dc733fe5c93ef5a795dde010152c63/Power.R

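### Excluding cognitive-task non-completers from Research Questions 2 to 4 drops usable physical-session data for a reason that does not hold in the mixed models, and can bias the Research Question 2 group effect.

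*Protocol article*

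**What the plan says.** The design has two sessions per person: "Participants will be asked to complete both sessions in a crossover design" (Experimental procedures), one with a cognitive task and one with a physical task, in random order.

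The Data inclusion and exclusion section sets this rule: "Participants failing to complete the cognitive task will be excluded from the analysis for Research Question 2, 3 and 4". The reason given is: "as we will not be able to compare the impact of task". The rule does not depend on why the task was not completed. The data are not lost to the study: "their data will be included in other exploratory analysis where the cognitive task is not included as a predictor". A second rule, for Research Question 3 only, removes people who withdraw before the post-task measures in either session.

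For Hypothesis 2 the Statistical analysis section says: "This will be tested using a linear mixed model". The outcome is state fatigue after exertion, indexed by group, task and subject. Task is one fixed effect beside group, baseline attenuation, baseline gating, fatigability and prior fatigue. Hypothesis 3 has the same row structure, with change in state fatigue and fatigability as predictors. Hypothesis 4 is confined to long COVID, has one row per person, and uses the cognitive-task fatigue increase as a predictor.

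On the battery itself, the Cognitive task section says: "The modified duration is expected to induce fatigue". It was shortened "to avoid placing excessive burden on a population that reports high fatigue levels".

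**The concern.** The rule removes a whole person because one of two sessions is incomplete. Someone who stops the cognitive battery but completes the walk test has an analysable physical session, and Research Questions 2 and 3 lose it.

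The loss is unlikely to be random. The battery is meant to cause fatigue, and the protocol itself ties its burden to this population's fatigue. Those who stop are plausibly the more fatigued members of the long COVID group. In Research Question 2 fatigue after exertion is the outcome, so removing such people lowers the long COVID mean and shrinks the group difference.

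The Sample size section concedes that "there is a potential for dropout to impact the subsequent research questions", but it does not consider that the loss may be selective.

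**Working it through.** **1. The plan's own figures.** For a two-sample t test with n per group, power comes from a noncentral t with 2n − 2 degrees of freedom and noncentrality d√(n/2). At n = 44 and two-sided alpha 0.05:

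- d = 0.78: noncentrality 0.78 × √22 = 3.66, power 95.1% (stated 95%; reproduced).
- d = 0.70: power 90.1% (stated 90%; reproduced).
- d = 0.60: power 79.5% (stated 80%; reproduced).

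The stated fall to 60% after 10% dropout is not reproduced: n = 40 per group gives 87.1% and 75.5%. It is not used below.

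**2. Does the stated reason hold?** With a participant-level random intercept, a person with only a physical row contributes to the group, attenuation, gating, fatigability and prior-fatigue terms. People with both rows supply the within-person task contrast. One-session participants do not prevent that comparison, so the reason fails for Hypotheses 2 and 3. It has more force for Hypothesis 4, where the missing cognitive-task increase is itself a predictor.

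**3. What can be kept.** Cognitive fatigability is scored from the first and last AX-CPT, and that task is also presented last. A stopped battery has no final AX-CPT, so its row lacks a model term. The physical row is complete.

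**4. Crude upper range for a selected mean.** Assume a normal fatigue response and that exactly the most fatigued fraction 1 − q of the long COVID group is lost. With z the q-quantile, the mean shift is −φ(z)/q and the remaining variance is 1 − zφ(z)/q − (φ(z)/q)².

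- 10% lost (q = 0.9, z = 1.28): shift −0.195 SD, variance 0.712.
- 20% lost (q = 0.8, z = 0.84): shift −0.350 SD, variance 0.583.

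**5. Hypothesis 2 by simulation; every input is assumed.** There are 44 per group and two sessions. Effects are group 0.70, attenuation 0.50, prior fatigue 0.50, and task (physical minus cognitive) −0.30. The participant and residual SDs are 0.7 each. Non-completers are the 4 (10%) or 9 (20%) long COVID participants ranked highest on cognitive-session fatigue plus noise of SD 0.5. The model has a participant random intercept and no fatigability terms. Means over 300 runs:

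| Non-completion | Term | Full data | Rule | Physical rows kept |
|---|---|---|---|---|
| 10% | group | 0.704 | 0.605 | 0.656 |
| 10% | attenuation | 0.496 | 0.469 | 0.485 |
| 10% | task | −0.296 | −0.266 | −0.249 |
| 20% | group | 0.715 | 0.512 | 0.628 |
| 20% | attenuation | 0.493 | 0.455 | 0.480 |
| 20% | task | −0.303 | −0.250 | −0.215 |

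Keeping the physical rows recovers about half of the lost group effect: (0.656 − 0.605)/(0.704 − 0.605) = 0.52 at 10%, and (0.628 − 0.512)/(0.715 − 0.512) = 0.57 at 20%. The task contrast moves slightly further from its true value, because the missing cognitive rows are the high ones.

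**6. Hypotheses 3 and 4.** Here fatigue change is a predictor. Simulated with a true slope of 0.40 and, for Hypothesis 3, a true group effect of 0.50, removing those with the largest fatigue increase left the Hypothesis 3 slope at 0.40 and its group effect at 0.51 (10%) and 0.50 (20%). The Hypothesis 4 slope stayed at 0.40, while its standard error rose from about 0.16 to 0.19 and 0.23.

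**7. Power.** If only the long COVID group loses people, 40 against 44 gives 88.6% at d = 0.70 and 77.5% at d = 0.60; 35 against 44 gives 86.3% and 74.4%. These losses are modest.

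**The case against.** Several stronger readings are tempting, and the document does not support them.

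- **Bias towards the null in all three questions.** Selection on the outcome describes only Research Question 2. In Research Questions 3 and 4 fatigue change is a modelled predictor, and selecting on it costs precision without biasing its slope (step 6). Research Question 4 has no control group, hence no long COVID effect to bias. Bias there needs stopping to depend on trait fatigue beyond the modelled predictors.
- **The data are thrown away.** They remain available for exploratory analyses.
- **The rule is arbitrarily asymmetric.** It has no direct counterpart for the physical task, but the walk test allows rests with the clock running, so non-completion is less of an issue there. The withdrawal rule for Research Question 3 covers either session.
- **A fatigue rating at stopping would rescue the cognitive row.** It would not supply the missing fatigability score, and it would mix ratings taken after different amounts of exertion.
- **A mixed model on all rows removes the bias.** That needs missingness at random. If stopping depends on fatigue that was not recorded, bias remains, as step 5 shows.
- **The 10% dropout figure gives the size.** That passage concerns failure to return for a second session, which is not the same as stopping the battery. The battery was cut from 120 to 24 minutes with patient input, and a training version is supplied; both should limit non-completion.

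These objections narrow the point. They leave standing that the stated reason fails for Hypotheses 2 and 3, and that usable physical rows are dropped in a way that can bias Research Question 2.

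**Conclusion.** The point holds for Research Question 2 as possible bias plus avoidable loss of data, and for Research Question 3 as avoidable loss of precision. In Research Question 4 the exclusion follows from using the cognitive-task increase as a predictor. Its cost there is precision, with bias only under the further condition named above.

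Under the assumed inputs, the rule lowers a Research Question 2 group effect of 0.70 to about 0.61 at 10% and 0.51 at 20% non-completion in the long COVID group. Keeping the physical rows gives about 0.66 and 0.63. These sizes rest on three assumptions: that stopping is driven by fatigue, that it occurs only in long COVID, and that the rates are as chosen. If few stop, or stop for unrelated reasons, the bias is small and what remains is a modest loss of precision.

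The rule should be changed before analysis. Research Question 1, for which the study is powered, is untouched.

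**What to change.** - **Hypotheses 2 and 3:** keep every analysable session, in particular the physical-session rows of cognitive-task non-completers. Drop only the incomplete cognitive row, because its fatigability score needs the last AX-CPT.
- **Random effect:** state a participant-level random intercept in both models. As printed, the subject-indexed term in Hypothesis 2 is not defined, and the random intercept in Hypothesis 3 is indexed by group.
- **Sensitivity analysis:** run the current complete-case rule as a sensitivity analysis. It also checks the task contrast, which keeping the extra rows can move.
- **Reporting:** give the number of non-completers by group, with reasons, and say that bias remains possible if stopping depends on unobserved fatigue.
- **Hypothesis 4 (optional):** as a sensitivity analysis, impute the missing cognitive-task increase from baseline, physical-task and partial numeric-rating data. Time-stamped ratings during the battery are already planned.

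The cost is a change of wording, some unbalanced data and a little extra analysis. No new data are needed.
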